### Statistical analysis

The main analysis adopts the intention-to-treat set, and all randomized subjects are included in the original allocation group; the per-protocol set analysis (PP) is used as a sensitivity analysis supplement. Categorical variables are presented as frequencies and percentages. Group differences will be assessed using Fisher’s exact test because of the small sample size. Continuous variables are subjected to Shapiro–Wilk normality test, and normal distribution data are analyzed using independent sample t-test (mean ± standard deviation), while non-normal data are analyzed using Mann–Whitney U test (median [IQR]). Missing data will be handled using multiple imputation with five imputations. In addition, worst-case and best-case scenario analyses will be conducted as sensitivity checks to assess the robustness of the results. For clinical events such as death, the intention-to-treat principle (ITT) are adopted, and cases of loss to follow-up are classified as no-event outcomes. Statistical analysis will be conducted using the Windows version 26.0 of SPSS statistical software (located in Ammonk, New York, produced by IBM Corporation).

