### Randomization

In this study, a computer-generated randomization sequence is used to allocate 40 participants to the RIC group and the control group (20 participants in each group) in a 1:1 ratio. Subsequently, the research assistant, who is not involved in the study, seals the group information in sequentially numbered opaque sealed envelopes according to the randomization sequence. All the random envelopes are uniformly stored in a confidential document cabinet before the start of the trial. After completing the participant enrollment screening and the collection of baseline data, the treating physician opens the random envelopes corresponding to the serial numbers and carries out the grouping operation according to the information contained therein.

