### Outcome

#### Safety outcomes assessment

The safety evaluation indicators are: (1) Mortality rate within 90 days. (2) Adverse events related to RIC (including limb skin injury, local pain, and deep vein thrombosis).

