#### Primary outcome measure

The primary outcome measures were the proportion of patients achieving a good functional outcome (mRS score 0–2) at 90 ± 7 days after surgery, and the incidence rate of RIC-related adverse events. The primary endpoint was assessed by blinded neurologists who were not involved in treatment allocation, using standardized interviews.

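### The RIC adverse-event rate, a primary outcome, falls under the intention-to-treat rule, so any patient allocated to RIC who never starts it would dilute the rate

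*Protocol article*

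**What the plan says.** Under Primary outcome measure, the article names two primary outcomes: the proportion with mRS 0–2 at 90 days "and the incidence rate of RIC-related adverse events". Safety outcomes assessment lists the same adverse events again and gives three kinds: skin injury of the limb, local pain and deep vein thrombosis.

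Statistical analysis then fixes the analysis set: "The main analysis adopts the intention-to-treat set, and all randomized subjects are included in the original allocation group". The only other set named is per-protocol: "the per-protocol set analysis (PP) is used as a sensitivity analysis supplement". The article does not say whom that set excludes. On events the section adds: "For clinical events such as death, the intention-to-treat principle (ITT) are adopted, and cases of loss to follow-up are classified as no-event outcomes". On the comparison of categorical outcomes: "Group differences will be assessed using Fisher’s exact test because of the small sample size".

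Randomization gives the size, which is to "allocate 40 participants to the RIC group and the control group (20 participants in each group) in a 1:1 ratio". According to Study design and Intervention, the RIC group has two sessions a day for 7 days (14 in all). Controls receive standard management, and no sham procedure is described.

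**The concern.** Intention-to-treat suits mRS and mortality, where the question is what follows from allocation to RIC. A RIC-related injury is a different kind of outcome, because only a patient who has had RIC can have one. A patient allocated to RIC who dies, deteriorates or declines before the first session adds one to the denominator and can add nothing to the numerator. Such patients can only lower the rate.

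This is more than a detail that the article leaves to a later document. It states a set for the main analysis, and one of the two primary outcomes fits that set badly. Safety is a stated aim of the trial, and Sample size estimation says that the results should inform the larger REPAIR trial. The rate carried forward should therefore describe patients who actually had the cuff inflated.

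**Working it through.** **Inputs from the article.** 20 patients per group (Randomization); analysis as allocated, with no outcome exempted (Statistical analysis); the RIC adverse-event rate is primary (Primary outcome measure). The article gives no expected adverse-event rate and no expected number of untreated RIC patients, so it has no figure of its own to reproduce here.

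**Assumed.** k, the number of RIC patients who never have a session, from 0 to 4; x = 4 patients with an event, all of them treated.

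**Dilution.** The rate in treated patients is x/(20 − k). The intention-to-treat rate is x/20, which equals the treated rate times (20 − k)/20.

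| k | factor | intention-to-treat | treated patients |
|---|---|---|---|
| 0 | 1.00 | 4/20 = 20.0% | 4/20 = 20.0% |
| 1 | 0.95 | 4/20 = 20.0% | 4/19 = 21.1% |
| 2 | 0.90 | 4/20 = 20.0% | 4/18 = 22.2% |
| 3 | 0.85 | 4/20 = 20.0% | 4/17 = 23.5% |
| 4 | 0.80 | 4/20 = 20.0% | 4/16 = 25.0% |

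Each untreated patient takes 5% off the value of the rate.

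**Against the sampling error.** The exact (Clopper–Pearson) 95% intervals are 5.7% to 43.7% for 4/20, 6.4% to 47.6% for 4/18 and 7.3% to 52.4% for 4/16. If no event is seen, the upper 95% limit is 16.8% with 20 patients, 18.5% with 18 and 20.6% with 16.

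**Fisher's test.** Assume no event without RIC. By allocation, 4/20 against 0/20 has one-tail probability C(20,4)/C(40,4) = 4845/91390 = 0.053. The opposite tail is equal, so p = 0.106. By treatment received with k = 2, the comparison is 4/18 against 0/22: C(18,4)/C(40,4) = 3060/91390 = 0.033. The opposite extreme, C(22,4)/C(40,4) = 7315/91390 = 0.080, is more probable than the observed table and is not added, so p = 0.033. Most of the fall comes from losing that second tail once the groups are unequal. It shows that the choice of set can matter near the 5% level; it does not measure the dilution.

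**The per-protocol set.** Take k = 2, which leaves 18 treated patients.
- If the set drops only the untreated, it gives 4/18 = 22.2%, the treated-patient rate.
- If it also drops two patients who stopped because of their event, it gives (4 − 2)/(18 − 2) = 2/16 = 12.5%.
- If it instead drops two who stopped without an event, it gives 4/(18 − 2) = 4/16 = 25.0%.

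The article does not say which applies, so the set cannot be relied on to supply the treated-patient rate.

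**The case against.** The intention-to-treat sentence is general and condensed. It does not mention adverse events, and a safety set is often defined in an analysis plan, which is not shown here. That explains the lack of detail, but the article does state a rule for the main analysis, and the rule takes in this primary outcome.

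The dilution may never occur. Patients are inpatients with consent given, the envelope is opened only after screening and baseline data are complete, and sessions are nurse-assisted and begin after enrolment. This stands: k may well be 0, and the article gives no reason to expect 2 to 4.

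Local pain and deep vein thrombosis also occur after surgery without RIC, so a randomised comparison is informative. This stands too. A set limited to patients with at least one cuff inflation would contain no controls if all keep to their allocation, so an exposed-only analysis cannot replace the comparison.

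Two stronger readings are tempting. A reader might infer from the open-label design, in which "the treating physician opens the random envelopes corresponding to the serial numbers and carries out the grouping operation", that controls could receive RIC and have their injuries counted against the control group. That sentence describes only how allocation is revealed, and nothing in the article shows or expects crossover. A reader might also infer that both named sets push the rate towards safety. For per-protocol this is not supported: its exclusions are not stated, and the working shows that the rate can move either way.

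**Conclusion.** The point holds as a poor fit between a stated rule and one primary outcome. The direction is certain: untreated RIC patients can only lower the intention-to-treat rate, by the factor (20 − k)/20. The size is not known. On assumed values it is 20% against 22% to 25% for k = 2 to 4 and four events, it is zero if every patient starts, and it is small beside an interval running from 5.7% to 43.7%. The documents do not show that any patient will go untreated, so it would be wrong to say that the rate will be understated. The change is worth making because it costs almost nothing and makes the reported rate mean what its name says.

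The no-event rule for patients lost to follow-up would lower the rate in the same direction if it is meant to cover adverse events. That is a separate matter, and this point does not rest on it.

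**What to change.** Add to Statistical analysis:

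- The RIC adverse-event rate is reported primarily among patients who received at least one RIC session, whether or not they completed the course, with its exact 95% interval.
- It is compared with all patients who received no RIC, grouped by treatment received. For this comparison the listed events should be counted alike in both groups, since an event judged related to RIC cannot by definition arise without it.
- The intention-to-treat comparison is kept as a supplement.
- mRS and mortality stay under intention-to-treat, and the per-protocol set is not relied on for adverse events.

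The cost is a few sentences and a record of whether each patient had a first session. The article does not describe session records, but it names compliance as a feasibility parameter and has the monitoring board review adherence, so the information should be at hand. The downside is a slightly less favourable rate if some patients never start, and a main safety comparison that is then no longer strictly as randomised; the supplement covers the latter. If all allocated patients start and no control has RIC, the two analyses coincide.

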## Methods

### Study design

We conduct an open-label, evaluator blinding, randomized controlled clinical trial in People’s Hospital of Ningxia Hui Autonomous Region and Beijing Tiantan Hospital on patients with aSAH who have undergone microsurgical clipping. Subjects who meet the inclusion criteria and do not meet the exclusion criteria will be randomly assigned to the RIC group and the control group within 24 h after microsurgical clipping, as shown in Figure 1. Both groups of subjects will undergo standardized and standardized management. The subjects in the RIC group will undergo remote ischemic preconditioning for 7 consecutive days after enrollment, once in the morning and once in the afternoon each day. The National Institutes of Health Stroke Scale (NIHSS) score will be blindly evaluated by trained researchers at the baseline. The Modified Rankin Scale (mRS) will be blindly evaluated by trained researchers on the 7th, 30th, and 90th days after enrollment.

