#### Secondary outcome measures

The incidence of aSAH complications.The mRS score of patients 7 ± 1 day after surgery.The mRS score of patients 30 ± 7 days after surgery.

This study adopts a blinded assessment design to ensure the objectivity of the data. The data collection and processing flow is as follows: All clinical data at baseline and during the follow-up period are collected by the attending physician and his team. The subjects are assigned a unique code (001-040) according to the order of enrollment. The core outcome indicators are verified by two research coordinators who are not involved in the management of the subjects and remained blinded to the group information, using a double-blind back-to-back assessment model to review the original data. If there are differences during the assessment, they will first be resolved through reviewing the original records and standardized judgment guidelines; if there are still differences, they would be submitted to a third independent assessor for arbitration. Finally, the result data and grouping information will be collected by a researcher and subjected to statistical analysis.

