This study has some limitations. Firstly, the RIC dose used in this study is determined based on the length of hospital stay of aSAH patients in clinical practice, although it is feasible in clinical practice, it has not been verified through dose exploration studies for the threshold of effect, and it may not be the optimal dose. Secondly, the subjects in this study are from two medical centers, and the population characteristics are relatively homogeneous, which may lead to selection bias and may affect the generalizability of the results. In addition, although randomization has balanced known confounding factors, there may still be baseline imbalance under a small sample size. Additionally, as the intervention involves limb ischemia, mild local discomfort or transient pain may occur. These aspects will be carefully monitored and reported to ensure patient safety and data integrity.

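### The day-90 mRS 0–2 comparison is fixed as an unadjusted Fisher test and leaves the baseline NIHSS and the ordinal mRS unused, at a cost in precision but not in validity

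*Protocol article*

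**What the plan says.** The article (Primary outcome measure) makes the efficacy endpoint "the proportion of patients achieving a good functional outcome (mRS score 0–2) at 90 ± 7 days after surgery". Its Statistical analysis section sets the population, "The main analysis adopts the intention-to-treat set, and all randomized subjects are included in the original allocation group", and one test for categorical variables: "Group differences will be assessed using Fisher’s exact test because of the small sample size". Continuous variables go through a Shapiro–Wilk test and then to a t-test or a Mann–Whitney test. No covariate-adjusted, stratified or ordinal comparison is named.

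Three other places bear on this:

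- Study design: "The National Institutes of Health Stroke Scale (NIHSS) score will be blindly evaluated by trained researchers at the baseline".
- Randomization: "After completing the participant enrollment screening and the collection of baseline data, the treating physician opens the random envelopes". Read with the previous line, this puts the NIHSS rating before allocation, although no single sentence says so. No stratification is described.
- Discussion, limitations: "although randomization has balanced known confounding factors, there may still be baseline imbalance under a small sample size".

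The mRS score itself is an outcome at the earlier visits, for example "The mRS score of patients 30 ± 7 days after surgery". At day 90 only the split at 2/3 is listed.

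**The concern.** The small sample is given as the reason for Fisher's test. But a small sample is also where chance differences in initial severity are largest and where each lost unit of information costs most. A blinded severity score recorded before allocation is the natural covariate, and the stated analyses leave it out. Cutting the day-90 mRS at 2/3 also discards the ordering within the good and poor categories, at the one time point that matters most.

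At stake is the precision of the efficacy estimate that this pilot passes on to the larger REPAIR trial, and the reader's ability to tell a treatment difference from a difference in case mix. The Sample size estimation section claims 0.80 power for this endpoint, so efficiency matters on the plan's own terms.

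**Working it through.** **Inputs from the article.** 20 per arm, 1:1; a 60% reduction in mRS>2, read as relative (p2 = 0.4·p1); α = 0.05, taken as two-sided; power 0.80; calculated minimum 18 per arm.

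**Not in the article, so assumed.** The control rate p1, the prognostic strength of NIHSS and the mRS distribution.

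**1. The plan's own figure.** The pooled formula is n = [1.96·√(2p̄q̄) + 0.842·√(p1q1 + p2q2)]² / (p1 − p2)². With p1 = 0.76, p2 = 0.304 and p̄ = 0.532, this is (1.383 + 0.528)² / 0.456² = 3.65/0.208 = 17.6, so 18. On a grid of 0.01, this formula gives 18 only at p1 = 0.76–0.77. The article does not say which formula or rate was used.

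**2. The named test, by full enumeration of the 2×2 tables at 20 per arm.**

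| Control rate of mRS>2 | RIC rate | Fisher power |
|---|---|---|
| 0.50 | 0.20 | 0.41 |
| 0.60 | 0.24 | 0.52 |
| 0.70 | 0.28 | 0.65 |
| 0.76 | 0.304 | 0.75 |
| 0.80 | 0.32 | 0.81 |

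Its true size is 0.020–0.025 for common rates of 0.3 to 0.6, against a nominal 0.05.

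**3. Chance imbalance.** A standardised baseline mean difference has SD √(1/20 + 1/20) = 0.316. The chance that it exceeds 0.5 SD in either direction is P(|Z| > 1.58) = 0.11; for 0.3 SD it is P(|Z| > 0.95) = 0.34. A logistic curve with slope β per SD rises by at most β/4 per SD. A 0.5 SD shift can therefore move the risk difference by at most 0.5 × 0.7/4 = 0.09 to 0.5 × 1.5/4 = 0.19 over the assumed slopes.

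**4. What adjustment adds.** Simulation at 20 per arm, with assumed rates of 0.70 and 0.28, a standard normal covariate with slope 0.7–1.5 log-odds per SD, and a linear model on arm, covariate and centre:

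| Analysis | Power | Null rejection |
|---|---|---|
| Fisher | 0.65–0.67 | about 0.02 |
| Linear, unadjusted | 0.75–0.77 | about 0.05 |
| Linear, adjusted | 0.81–0.88 | 0.046–0.058 |

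A repeat with 8,000 trials per setting gave adjusted power of 0.79, 0.83 and 0.87 at slopes 0.7, 1.0 and 1.5, so the lower end is best read as about 0.8. The first step, from Fisher to the unadjusted model, is about 0.10. The second, from adjustment, is 0.81 − 0.76 = 0.05 up to 0.88 − 0.75 = 0.13. With a covariate of no prognostic value, adjusted and unadjusted power were the same to within 0.01.

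**5. Choice of model.** Ordinary logistic regression with a likelihood-ratio test rejected in 0.058–0.070 of null trials. The linear model with one covariate rejected in 0.048–0.056.

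**6. Ordinal day-90 mRS.** Under an assumed distribution and proportional odds, power for Mann–Whitney against Fisher is 0.66 against 0.41 at a control rate of 0.50, 0.76 against 0.52 at 0.60, and 0.92 against 0.76 at 0.76. Null rejection is about 0.05 against 0.02.

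**The case against.** The strongest reply is that nothing here is an error. Fisher's test protects type I error, a randomised comparison without covariates is unbiased on average, and the cut at mRS 0–2 is used consistently. Supportive adjusted analyses are often left to a statistical analysis plan, which is not shown, and the trial is a pilot. All of this stands, with one limit: the choice of Fisher is stated with a reason, so it is a decision made in the text and open to comment.

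Four stronger readings are tempting, and the article does not support them.

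- *The result will be biased or the test invalid.* It will not. The test errs on the cautious side.
- *Baseline imbalance is expected.* The limitations paragraph says only that "there may still be baseline imbalance under a small sample size".
- *The whole power gap is the price of ignoring NIHSS.* About 0.10 of it arises because Fisher works at a true level near 0.02 while the comparators work near 0.05.
- *NIHSS will never be used.* The article names no use in the between-group tests; a fuller document might.

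It is also fair to say that a model in 40 patients carries its own risk, and that replacing an exact test with a loosely described model would be no improvement. Mann–Whitney is already available for mRS at days 7 and 30, but only if a normality test rejects.

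**Conclusion.** The point holds as one of efficiency and of uncorrected chance imbalance. The plan commits to an unadjusted, conservative test on a dichotomy while a blinded baseline severity score, apparently recorded before allocation, and the ordinal day-90 score go unused in the stated comparisons.

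The direction of the loss is the same in every setting tried with a prognostic baseline. Its size is illustrative only, since it depends on a control rate, a prognostic slope and an mRS distribution that the article does not give. The conservatism of Fisher's test at 20 per arm needs none of the assumptions about NIHSS. The change is worth making because it is cheap, not because the planned test would mislead.

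**What to change.** - Pre-specify a risk difference in mRS 0–2 at day 90 with 95% CI from one fully specified small-sample model. One example is linear regression on arm, continuous baseline NIHSS and centre, with a t reference on 40 − 4 = 36 degrees of freedom. Report it alongside Fisher's test, and say in advance which of the two carries the conclusion.
- Avoid ordinary logistic adjustment, or penalise it, given null rejection of about 0.06–0.07.
- Add the full ordinal day-90 mRS as a secondary outcome, analysed by Mann–Whitney.
- Analyse mRS at days 7 and 30 as ordinal as well, and not by a t-test chosen through Shapiro–Wilk.
- State outright that baseline NIHSS is recorded before the envelope is opened.

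The cost is wording and a little more analysis, with no new visits, data or patients. The downside is some reliance on a model in 40 patients, which keeping Fisher beside it limits. These choices should be fixed before outcome data are seen by arm.

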### Sample size estimation

Previous studies have shown that a sample size of 10-20 cases per group in a randomized controlled clinical trial is sufficient to fully meet the requirements (22) for feasibility assessment (including core parameters such as recruitment efficiency and intervention compliance). This range is in line with the efficacy calculation standards for pilot studies, and can effectively balance the requirements of scientific research ethics and resource optimization allocation. Assuming a 60% reduction in poor outcomes (mRS>2) in the RIC group compared with controls at 90 ± 7 days after surgery, the sample size calculation indicated that 18 patients per group were required. Thus, 20 patients per group (*n* = 20) were planned for enrollment (α = 0.05, power = 0.80). The calculated minimum sample size was 18 participants per group. Therefore, our goal is to recruit 20 patients per group. The results of this study should be able to determine the initial safety, feasibility, and effectiveness of RIC in aSAH patients, providing good guidance and reference for further conducting large-scale randomized double-blind clinical studies (REPAIR).

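### Fisher's exact test is valid but needlessly conservative for the primary mRS 0–2 comparison: with 20 analysed per arm its true size is at most 2.5% against the stated 5%, and an unconditional exact test would recover power

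*Protocol article*

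**What the plan says.** - Primary efficacy outcome (Protocol article, Primary outcome measure): "the proportion of patients achieving a good functional outcome (mRS score 0–2) at 90 ± 7 days after surgery". This is a binary endpoint.
- Allocation (Randomization): the sequence is to "allocate 40 participants to the RIC group and the control group (20 participants in each group) in a 1:1 ratio".
- Sample size (Sample size estimation): "Assuming a 60% reduction in poor outcomes (mRS>2) in the RIC group compared with controls", with "α = 0.05, power = 0.80". "The calculated minimum sample size was 18 participants per group", raised to 20. No control-arm rate, sidedness or formula is given.
- Test (Statistical analysis): group differences in categorical variables are to be assessed by Fisher's "exact test because of the small sample size". The same section makes the intention-to-treat set the main analysis, with five multiple imputations for missing data.

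**The concern.** A small sample is a good reason for an exact test. It is not a reason for this particular one. Fisher's test conditions on both margins of the 2×2 table, but the design fixes only the arm totals; the number of patients reaching mRS 0–2 is random. At small sample sizes this conditioning leaves few attainable p-values, so the real error rate falls well below the nominal level.

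Boschloo's test uses the Fisher p-value only to order the tables, then calibrates the cut-off so that the type I error is at most 5% whatever the common event rate. Its rejection region contains Fisher's, so it cannot lose power. At stake is power that a 40-patient trial could keep at no cost in patients or α, and whether the stated power of 0.80 applies to the test that will be run.

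**Working it through.** **Inputs.** From the article: 20 per arm, α = 0.05, target power 0.80, and a 60% reduction in poor outcome (mRS > 2), read as a relative risk of 0.40. Assumed because not stated: two-sided testing and the control poor-outcome rate pc (range shown). The RIC rate is 0.4 × pc.

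**1. The plan's figure of 18 per group.** It cannot be reproduced without a control rate, so I looked for the rate that returns it. The two-sided pooled formula is

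n = [1.960 √(2p̄(1−p̄)) + 0.842 √(p₁(1−p₁) + p₂(1−p₂))]² / (p₁−p₂)².

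With p₁ = 0.76, p₂ = 0.304 and p̄ = 0.532, the numerator is (1.960 × √0.498 + 0.842 × √0.394)² ≈ 3.653 and the denominator is 0.456² = 0.208. So n ≈ 17.6, rounded up to 18. The same holds at 0.77. Other formulas return 18 at other rates: unpooled two-sided at 0.71–0.72, one-sided pooled at 0.67–0.68, two-sided with continuity correction at 0.83–0.84.

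**2. True size at 20:20.** For a rejection region R, size = max over p of Σ over (a,b) in R of Bin(a; 20, p) × Bin(b; 20, p), enumerating all 21 × 21 tables.

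- Fisher (p ≤ 0.05): 2.26% at a common rate of 0.2, 2.48% at 0.3, 2.38% at 0.4, 2.04% at 0.5. The maximum is 2.53%, at about 0.34 or 0.66.
- Boschloo: the largest admissible Fisher-p cut-off is 0.0915, with a maximum size of 4.6%. Admitting the next table would give 5.3%.

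**3. Power at relative risk 0.40, 20:20.** Same sum, with pc and 0.4 × pc in place of the common rate.

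| Control poor-outcome rate (assumed) | Fisher | Boschloo | Gain (points) |
|---|---|---|---|
| 0.30 | 18.6% | 27.3% | 8.7 |
| 0.40 | 28.8% | 38.5% | 9.6 |
| 0.50 | 40.9% | 49.2% | 8.3 |
| 0.60 | 52.4% | 61.6% | 9.2 |
| 0.70 | 65.3% | 75.2% | 9.9 |
| 0.76 | 74.7% | 82.8% | 8.1 |
| 0.80 | 81.3% | 87.4% | 6.2 |
| 0.90 | 94.6% | 96.6% | 2.0 |

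Gains are taken before rounding. At a rate of 0.20 the gain is 4 points. If α = 0.05 is one-sided, Fisher's size is 2.7% and the gain is 8 to 9 points for rates 0.30–0.70, 7 at 0.75 and 5 at 0.80.

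**4. Sensitivity to the analysed split (control:RIC), rates 0.30–0.76.** At 19:20 and 20:19 Fisher's size is 3.6% and Boschloo gains 0 to 4 points. At 18:20 the gain is 1 to 4 points. At 20:18 the same enumeration gives 1 to 7 points. At 18:18 it is 7 to 11 points for rates 0.40–0.60 but only 3 to 4 for 0.70–0.80.

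**5. Which results change.** Poor outcomes of 12 v 5 (reduction 1 − 5/12 = 58%) give Fisher p = 0.054 and Boschloo p = 0.030. Also reclassified are 13 v 6 (54%), 14 v 7 (50%) and 15 v 8 (47%), as well as larger effects such as 9 v 3 (67%, Fisher p = 0.082). The four tables with exactly a 60% reduction do not change: 10 v 4 is non-significant under both (0.096 and 0.053), 15 v 6 is significant under both (0.010 and 0.006), and 5 v 2 and 20 v 8 also agree.

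**The case against.** The strongest reply is that nothing here is wrong. Fisher's test keeps its error at or below 0.05, it is a standard choice for small tables, and whether to condition on both margins is a long-standing matter of preference. That stands: the point is efficiency, and a size below the nominal level does not contradict the stated α.

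The gain also depends on the analysed numbers. It is largest near exact 20:20 balance, and one missing patient can cut it to between 0 and 4 points. This stands and limits the claim.

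If any 90-day mRS is missing, the main analysis is not one table but five imputed ones, and there is no standard rule for pooling exact p-values under either test. This stands too; naming a different test does not by itself settle it.

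A reader might infer that data matching the planned effect would be missed because of Fisher's test. The tables with exactly a 60% reduction do not bear that out; only neighbouring ones change.

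A reader might also infer that the stated 0.80 is shown to be false. The article does not give the control rate or formula needed to show that. On the two-sided pooled reading Fisher falls short (74.7%). On the two-sided continuity-corrected reading (0.83–0.84) it does not: Fisher's power with 20 per arm is 84.4% at 0.82 and 88.8% at 0.85.

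Finally, this is a pilot meant to inform a larger trial, which lowers the stakes. It does not remove them, since the article itself sets an α, a power and a primary efficacy comparison.

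**Conclusion.** The point holds as an avoidable loss of efficiency. With 20 analysed per arm, the two-sided Fisher test runs at no more than about half the stated α (2.5%). Boschloo's test stays within 5% (4.6%), never rejects less often, and adds about 8 to 10 points of power for a 60% relative reduction at control poor-outcome rates of 0.30–0.76, and 6 points at 0.80. This rests on assumed control rates, assumed two-sided testing and complete 20:20 data; at 19:20 or 18:20 the gain is about 0 to 4 points.

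The power statement should be tied to the test and to a stated control rate. On the two-sided pooled reading, the choice of test decides whether 20 per arm reaches 0.80. Changing the test does not rescue the power in general: at control rates up to 0.70 both tests remain below 0.80. The documents do not support calling Fisher's test invalid or the type I error inflated. The change is advisable rather than essential.

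**What to change.** 1. In Statistical analysis, prespecify Boschloo's exact test, two-sided 0.05, for the primary mRS 0–2 comparison, before outcomes are seen by arm. Do not offer mid-P Fisher as an alternative: its result depends on the version used, and at 19:20 the versions tried reached 5.3%.
2. Report the risk difference with a 95% confidence interval beside the p-value.
3. State how the result is obtained when mRS is multiply imputed, for example the exact test on observed data together with the pooled risk difference from the imputed sets.
4. In Sample size estimation, state the assumed control poor-outcome rate and the sidedness, and restate the power for the test actually used.

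Cost: a few sentences, no extra patients and no relaxation of α. The test may need software other than the named SPSS version (it is a single function call in Python), and the benefit is small if the analysed arms end up unequal.

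### Scoring patients lost to follow-up as event-free can only understate absolute 90-day mortality, and the rule is not reconciled with multiple imputation

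*Protocol article*

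**What the plan says.** All the missing-data rules stand in one paragraph of the protocol article, under Statistical analysis.

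- Analysis set: "The main analysis adopts the intention-to-treat set, and all randomized subjects are included in the original allocation group".
- General rule, with no outcome excepted: "Missing data will be handled using multiple imputation with five imputations".
- Sensitivity: "worst-case and best-case scenario analyses will be conducted as sensitivity checks to assess the robustness of the results".
- Rule for events: "For clinical events such as death, the intention-to-treat principle (ITT) are adopted", and in the same sentence "cases of loss to follow-up are classified as no-event outcomes".

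Under Safety outcomes assessment, the first item is "Mortality rate within 90 days" and the second is "Adverse events related to RIC (including limb skin injury, local pain, and deep vein thrombosis". The Primary outcome measure section names RIC-related adverse events again, next to mRS 0–2 at 90 days: "and the incidence rate of RIC-related adverse events". The incidence of aSAH complications is a secondary outcome.

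**The concern.** Intention-to-treat settles who is analysed and in which arm. It does not supply a value for a patient whose outcome is unknown. Scoring that patient as event-free fills the gap with the most favourable value and treats it as observed, so the uncertainty from the loss disappears from the result.

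Safety is the first aim that the article names, and the trial is meant to inform the larger REPAIR trial. A mortality figure that can err only downward is a poor basis for that step, and in an arm of 20 a single patient moves it visibly.

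The paragraph also leaves two rules side by side. A missing death status falls under the general imputation rule and under the no-event rule, and nothing says that the second is an exception to the first. The wording of the event rule gives death only as an example, so its reach into RIC-related adverse events and aSAH complications is open.

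**Working it through.** **Inputs.** From the article: 20 patients per arm, and the no-event rule. The article states neither an expected mortality nor an expected loss rate, so there is no planned figure to reproduce. The values below are assumptions, shown as a range.

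**Absolute rate in one arm.** Let p be the true event risk in the arm, l the share lost and q the risk among the lost. The rule counts none of the events among the lost, so

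recorded risk = p − l × q.

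Since l × q cannot be negative, the recorded risk is never above p.

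| True mortality p | Loss l | Recorded if q = p | Recorded if q = 2p |
|---|---|---|---|
| 10% | 5% | 9.5% | 9% |
| 10% | 10% | 9% | 8% |
| 10% | 20% | 8% | 6% |
| 20% | 5% | 19% | 18% |
| 20% | 10% | 18% | 16% |
| 20% | 20% | 16% | 12% |
| 30% | 5% | 28.5% | 27% |
| 30% | 10% | 27% | 24% |
| 30% | 20% | 24% | 18% |

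Example: p = 20%, l = 10%, q = 20% gives 0.20 − 0.10 × 0.20 = 0.18. When q = p, the relative understatement equals the loss fraction. In whole patients, one hidden death is 1/20 = 5 percentage points of an arm.

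**Contrast between arms.** Take true mortality of 20% in both arms, with q = p.

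- Loss 20% in RIC and 5% in control: 0.20 × 0.80 = 16% against 0.20 × 0.95 = 19%, a spurious 3-point advantage for RIC.
- The same losses with the arms exchanged: 19% against 16%, a spurious 3-point disadvantage.
- Equal loss in both arms: both rates shrink by the same factor and the risk ratio is unchanged.

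**A constructed extreme, to show what the rule can hide.** RIC has 6 deaths and 4 lost; control has 2 deaths and none lost.

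- Under the rule: 6/20 = 30% against 2/20 = 10%, Fisher p = 0.24.
- Observed cases: 6/16 = 37.5% against 10%.
- Lost counted as deaths: 10/20 = 50% against 10%, Fisher p = 0.014.

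**The two rules side by side.** Suppose that a lost patient's 90-day mRS is imputed on the full scale and comes out as 6, which is death. The functional analysis then counts the patient as dead, while the mortality table counts the same patient as alive. This follows even if the event rule is read as a deliberate exception to imputation.

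**The case against.** Several points on the other side stand.

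- **A reader might infer a flat contradiction with multiple imputation.** The text does not go that far. A general rule followed by a specific one for events can be read as rule and exception. The functional primary outcome is mRS 0–2 or not, and an imputed poor outcome of mRS 3–5 is compatible with being alive. The clash arises only for an imputed 6, and the article does not say on which scale imputation is done.
- **A reader might infer that the rule favours RIC.** That holds only if loss, or risk among the lost, is higher in the RIC arm. The reverse pattern works against RIC.
- **A reader might take the step from 18 to 20 per group as a 10% loss allowance.** The Sample size estimation section never links that step to attrition, so the 10% used here is only an assumption.
- **Adverse events are probably little affected.** RIC is given over 7 days with nurse assistance, so skin injury and local pain would mostly be seen before anyone is lost. Deep vein thrombosis could come later.
- **Safeguards exist.** Best- and worst-case analyses are planned with no outcome excluded. The DSMB reviews adverse events and data completeness every three months, and serious events are reported within 24 h. Protection of participants does not rest on this rule.
- **Censoring is no complete cure.** If 10% are lost early and die at 40%, while the retained die at 20%, the truth is 0.90 × 0.20 + 0.10 × 0.40 = 22%. Kaplan-Meier would estimate about 20%, and the no-event rule records 18%.

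None of this changes the main mortality analysis, which still carries the most favourable value for every lost patient.

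**Conclusion.** The point holds for absolute rates. As written, the rule cannot overstate 90-day mortality in either arm, and it understates it whenever a lost patient has died. This is a stated rule that is wrong, not a detail left to another document. Under the assumed ranges (true mortality 10–30%, loss 5–20%, risk among the lost equal to or twice the overall risk), the understatement runs from 0.5 to 12 percentage points. At 20% mortality and 10% loss it is 2 to 4 points. If no one is lost, or if vital status is known for everyone, it is nil.

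The direction of any bias between arms cannot be told from the article. The overlap with multiple imputation is a failure to reconcile two rules rather than a proven contradiction, and the reach into adverse events and complications is unclear. Mortality is a safety outcome and not one of the two primary outcomes. For a 40-patient pilot with sensitivity analyses and a DSMB, this is a change that should be made, not one on which the trial stands or falls.

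**What to change.** 1. Remove no-event as the main rule for patients lost to follow-up, and keep it only as the best-case scenario for event rates.
2. For the main mortality analysis, treat lost patients as missing, censor them at the date last known alive (Kaplan-Meier), or impute them consistently with the 90-day mRS, with death scored as 6.
3. State which missing-data rule covers which outcome: functional mRS, mortality, RIC-related adverse events and aSAH complications.
4. State that the planned best- and worst-case analyses include mortality and adverse events, with a scenario that counts lost patients as events. This is needed whichever main method is chosen, because censoring alone does not remove informative loss.

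The cost is a few lines of analysis wording, recording a last-known-alive date for each patient, and slightly wider intervals.
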